### Sample size

In order to provide a power of 95% with 95% confidence interval the following formula and the standard deviation of 3.17 to 3.21 (according to the same study’s findings) will be used [18]. The sample size was estimated at 30, and then allowing for 10% attrition, we plan to recruit 33 samples per group and a total of 66 study participants.$$ n=\frac{{\left({z}_{1-\frac{\alpha }{2}}+{z}_{1-\beta }\right)}^{2}\left({s}_{1}^{2}+{s}_{2}^{2}\right)}{{\left({\overline{x}}_{1}-{\overline{x}}_{2}\right)}^{2}}$$$$ \frac{{\left(1.96+1.64\right)}^{2}\left({3.21}^{2}+{3.17}^{2}\right)}{{3}^{2}}=29.4\cong 30$$$$ 30+30\left(0.1\right)=33$$

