## Methods

### Study design

A cluster randomized controlled trial will be carried out on breastfeeding mothers referred to health centers affiliated to Tehran University of Medical Sciences. A cluster randomized controlled trial design was chosen because it makes it easier for mothers to attend classes at their local health center, and in this design, the phenomenon of contamination between the intervention and control groups is avoided. Besides, it can help us increase the representativeness and generalizability of our study population and results. The control group allows us to analyze the direct effect of the intervention and discount an increase in milk donation due to other factors [20]. This study was approved by the Research Ethics Committees of School of Nursing and Midwifery & Rehabilitation - Tehran University of Medical Sciences (IR.TUMS.FNM.REC.1401.150).

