### Setting

This study will be conducted in health centers affiliated to Tehran University of Medical Sciences. Tehran University of Medical Sciences covers primary health care services of 5 out of 22 districts of Tehran City (district numbers 10, 11, 16, 17 and 19) [21]. These health centers were chosen because they cover a significant portion of breastfeeding mothers of South Tehran, who usually bring their infants to theses\ health centers for vaccination, screening or growth monitoring. However, we will include four of these districts in our study (district numbers 10, 11, 16 and 17) because the health centers of district number 19 do not have the equipment for holding in-person classes and the population of Iranian breastfeeding mothers in that district is limited. These four districts have a total of 20 health centers. From among all these health centers, we will choose eight centers using simple randomization method; then, a cluster of four centers will be randomly selected for collecting the intervention group and four centers for collecting the control group. We will recruit eight to nine participants from each health center.

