### Statistical analysis

We will use descriptive analysis to report baseline characteristics. In this study the Repeated ANOVA between subjects test will be used for quantitative variables which have a normal distribution, and the Friedman test will be used for quantitative variables that do not have a normal distribution. For qualitative variables, chi-square test or Fisher’s exact test will be used. The effectiveness of the intervention will be assessed using the repeated measure ANOVA test and the effect of demographic variables on milk donation behavior will be determined using a logistic regression model. Statistical analyses will be made using IBM-SPSS 22. The trial has been registered at the Iranian Registry of Clinical Trials (IRCT20230124057203N1).

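### The stated 95% power treats mothers as individually randomised, but the trial randomises eight health centers and no clustering enters the calculation

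*Protocol article*

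**What the plan says.** The Study design section describes the trial as cluster randomised: "A cluster randomized controlled trial will be carried out on breastfeeding mothers referred to health centers affiliated to Tehran University of Medical Sciences". The Setting section gives the numbers. Eight of 20 centers are drawn, and then "a cluster of four centers will be randomly selected for collecting the intervention group and four centers for collecting the control group". It adds: "We will recruit eight to nine participants from each health center".

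The Sample size section claims 95% power from a printed formula: "In order to provide a power of 95% with 95% confidence interval the following formula and the standard deviation of 3.17 to 3.21". The formula is the usual one for two independent means, with z values 1.96 and 1.64 and a difference of 3. The result is carried forward as follows: "The sample size was estimated at 30, and then allowing for 10% attrition, we plan to recruit 33 samples per group". Attrition is the only inflation.

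For the comparison of arms, the Statistical analysis section says: "The effectiveness of the intervention will be assessed using the repeated measure ANOVA test". It names no center term and no center-level test.

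**The concern.** The formula assumes that each mother contributes independent information. Mothers at the same center may resemble one another, and those in the intervention arm also attend sessions held at their centers. If outcomes are correlated within centers, the variance of an arm mean is multiplied by a design effect above 1. With only four randomised units per arm, a valid test also has few degrees of freedom. Neither feature is in the calculation.

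What is at stake depends on the analysis. If the analysis respects the centers, the chance of missing the planned effect is well above 1 in 20, and a null result read against a claimed 95% would look stronger than it is. If the analysis treats mothers as independent, the main risk is a false positive.

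**Working it through.** **Inputs from the Protocol article.** SDs 3.21 and 3.17, difference 3, z values 1.96 and 1.64, 30 analysed and 33 recruited per arm (Sample size); 4 centers per arm (Setting). Hence m = 30/4 = 7.5 analysed mothers per center. The document gives no ICC, so 0 to 0.20 is an assumed range.

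**1. The plan's own figure.** (1.96 + 1.64)² × (3.21² + 3.17²) / 3² = 12.96 × 20.353 / 9 = 29.3; with unrounded z values, 29.4. Rounded up, this is 30 per arm, as stated. With SD = √(20.353/2) = 3.19, power at 30 per arm is 95.4% by the normal approximation and 94.8% by a t-test on 58 df. The stated 95% therefore reproduces for 60 independent mothers.

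**2. Design effect.** DE = 1 + (7.5 − 1) × ICC. The standard error of the arm difference is SE = 3.19 × √(2 × DE / 30). At ICC 0.05, DE = 1.325, SE = 0.948 and 3/SE = 3.16.
- Normal approximation (design effect only): power = Φ(3/SE − 1.96).
- Center-level test: noncentral t with 2 × (4 − 1) = 6 df, noncentrality 3/SE and critical value 2.447.

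| Assumed ICC | DE | Effective n per arm | Power, design effect only | Power, center-level, 6 df |
|---|---|---|---|---|
| 0 | 1.000 | 30.0 | 95.4% | 85.6% |
| 0.01 | 1.065 | 28.2 | 94.2% | 83.5% |
| 0.02 | 1.130 | 26.5 | 92.9% | 81.3% |
| 0.05 | 1.325 | 22.6 | 88.6% | 75.1% |
| 0.10 | 1.650 | 18.2 | 80.9% | 65.9% |
| 0.20 | 2.300 | 13.0 | 67.1% | 52.2% |

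If all 33 per arm are retained (m = 8.25), the design effect alone gives 95.8%, 90.5% and 82.9% at ICC 0.01, 0.05 and 0.10. The 6-df figures are then 86.5%, 77.8% and 68.1%.

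**3. Ignoring centers in the analysis.** A mother-level t-test was simulated with 30 per arm in centers of 8, 8, 7 and 7. At nominal 5%, the type I error is about 5.8%, 8.9% and 12.9% at ICC 0.01, 0.05 and 0.10. The rejection rate under the planned difference is about 92% at ICC 0.05 and 90% at 0.10. Those rates are not power at the 5% level, because the test no longer holds that level.

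**4. What baseline adjustment could recover.** Multiply SE by √(1 − r²), where r is the correlation between baseline and follow-up scores, and keep 6 df. The document gives no r. At an assumed r = 0.5 the factor is √0.75 = 0.866, and power is about 94%, 86% and 78% at ICC 0, 0.05 and 0.10. At ICC 0.05, r = 0.3 gives about 79% and r = 0.7 about 96%.

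**The case against.** The strongest objection is that the 6-df figures belong to a test the protocol does not name. The Statistical analysis section plans repeated-measures ANOVA. If there were truly no between-center variation, a mother-level comparison would be valid and would have 94.8% power. This stands. A reader might infer that the design misses 95% even with no clustering at all, but that is true only if a center-level analysis is used. The 86% at ICC 0 is the price of a test that stays valid when the ICC is unknown. At very low ICC the design effect matters little: at 0.01 with all 33 retained, the normal approximation still gives 95.8%.

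A second objection is that repeated measures or the baseline score may recover power. This stands in part. The Sample size section claims no such gain and gives no correlation. A reader might also take baseline adjustment to be planned, because a baseline assessment is collected, but the document names no baseline-adjusted model.

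A third is that a journal article condenses the full protocol. That does not help here: the calculation is printed from 29.4 to 30 to 33, with attrition as its only inflation, so the text leaves no place for an unreported allowance for clustering.

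**Conclusion.** The point holds. The Sample size section claims a power that applies to independently randomised mothers, not to four centers per arm. This is an omitted design assumption; the printed arithmetic is sound.

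The direction is certain for any ICC above 0, while the size is not. With 30 analysed per arm and a center-level analysis, power is about 81% at ICC 0.02, 75% at 0.05, 66% at 0.10 and 52% at 0.20. With the design effect alone it is 88.6% at 0.05 and 80.9% at 0.10. All of these rest on the plan's own difference and SD, on a single follow-up comparison without baseline adjustment, and on assumed ICCs. None should be read as the true power of this trial.

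A reader might conclude that the main danger is a null result taken as proof that the program fails. That follows only if the analysis respects the centers. As the Statistical analysis section stands, with no center term, inflated type I error is at least as important.

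**What to change.** Two linked changes are needed; either one alone would leave the sections inconsistent.

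1. **Sample size.** Replace the 95% with the power under clustering. State an assumed ICC with a range and its rationale, the design effect 1 + (7.5 − 1) × ICC, the 6 df and the resulting power (for example about 75% at ICC 0.05, with the range shown).
2. **Statistical analysis.** State that the arm comparison accounts for center, either by center-level summaries or by a mixed model with a small-sample df correction.

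Adjustment for the baseline score already collected can be added as a new proposal, with its assumed correlation and a range. It should not be described as already planned.

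The cost is a less favourable stated power and a little more analysis work. These two changes need no extra mothers, but they do not restore 95%. If 95% is to be kept without baseline adjustment, more centers are the main route. At 7.5 analysed mothers per center and df = 2(k − 1), about 7 centers per arm are needed at ICC 0.05 and 8 at 0.10, that is 14 and 16 of the 20 centers in the Setting section. That is a separate decision about resources.

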### Development of the educational intervention

In this study, the educational intervention is designed by reviewing literature comprising guidelines and statements on donor milk, human milk bank, storage and preparation of breast milk and the importance of breast milk from the following sources: Human Milk Banking Association of North America (HMBANA), European Milk Bank Association (EMBA), World Health Organization (WHO), United Nations Children’s Fund (UNICEF), Centers for Disease Control and Prevention (CDC), and American Academy of Pediatrics (AAP) [22–24]. We also used the Human Milk Bank Clinical Guideline in Iran, which covers various aspects such as the infrastructure, awareness, communication, ethical issues, donors, recipients, and working processes of a human milk bank [25].

After that, we applied the Delphi method to gather and validate the material according to the opinions of experts in midwifery and reproductive health and neonatology of Tehran University of Medical Sciences. We conducted three rounds of questionnaires with the panel, which consisted of three neonatologists, three midwives who have experience in breastfeeding education, one health education professional, and one midwife who was in charge of a milk bank. They were well informed and familiar with the Iranian culture and community, especially regarding the issues of milk kinship and the role of the husband and families in Iranian mothers’ milk donation, and breastfeeding mothers’ skills and self-efficacy in expressing their breast milk.

### Intervention design

Following baseline data collection, the intervention group will start receiving 60-minute weekly educational intervention based on TPB components for four weeks (Table 1).

**Table 1 Tab1:** The content of the educational sessions based on the theory of planned behavior

Session	Main purpose	Educational materials	Educational methods and time schedule
1	Improving breastfeeding mothers’ knowledge and attitudes toward DHM and HMB	• PowerPoint presentation • Booklet (including contents of all sessions) • Pamphlet of the first session	1) Introducing presenter and participants and explaining study aims (10 min) 2) Giving information on importance and background of breast milk donation and HMBs (40 min) 3) Question and answer (10 min)
2	Addressing the role of subjective norms in breast milk donation	• PowerPoint presentation • Pamphlet of the second session	1) Reviewing previous session (5 min) 2) Giving information related to Islamic laws of milk donation (15 min) 3) Presenter will use the psychodrama method. In this method two volunteer breastfeeding mothers role-play problems and release their intense emotions in regard to milk donation, then the presenter will guide their subjective norms [26] (30 min) 4) Question and answer (10 min)
3	Addressing the role of perceived behavioral control in breast milk donation behavior	• PowerPoint presentation • Pamphlet of the third session • Video	1) Reviewing previous session (5 min) 2) Giving information on requirements for breast milk donation, indication and contraindication of breast milk donation, process and cost of HMBs and current status of HMBs in Tehran (40 min) 3) Screening a video which shows how a HMB works (5 min) 4) Question and answer (10 min)
4	Addressing the behavioral intention and explaining how to implement the behavior of donating breast milk	• PowerPoint • Pamphlet of the fourth session • Video • Breast pump	1) Reviewing previous session (5 min) 2) Giving information on breast milk expression (10 min) 3) Showing how to express breast milk by hand and breast pump (25 min) 4) Showing videos of successful breast milk expression (10 min) 5) Question and answer (10 min)

Lectures, small groups discussion, educational pamphlets and booklet, PowerPoint presentations, showing videos and pictures, will be the main educational methods and materials that we are going to use in order to make the program effective and interesting. Moreover, we will ask mothers to share the booklet and pamphlets with their family and friends. Sessions will be held in health centers for the intervention group while the control group will receive only usual education.

### Data collection

The questionnaire will be uploaded to Porsline, a well-known online survey platform in Iran, to create a link for the questionnaire. Participants can use their mobile phones to open the link and fill out the questionnaire. A baseline assessment will be conducted prior to the intervention for both the intervention and control groups. In order to assess the immediate and long-term effects of the intervention prospectively, the first follow up assessment will be conducted immediately after the intervention, and the final one will be conducted 12 weeks later. Our primary outcomes are the number of mothers who have donated their breast milk and changes that have happened in breastfeeding mothers’ knowledge, attitudes, subjective norms, perceived behavioral control about DHM and intention to donate milk. Our secondary outcomes are the associations of behavioral determinants and social demographic variables with milk donation.

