### Objectives

The main objective of this study is to assess the effectiveness of an educational intervention based on TPB in breastfeeding mothers on donating breast milk to HMBs.

Secondary objectives of the study are:

To evaluate changes in breastfeeding mothers’ knowledge about milk donation.To evaluate the effect of the educational program on behavioral determinants (attitude, subjective norms, perceived behavioral control and behavioral intention).To analyze the association of behavioral determinants with milk donation.To study the relationship between social demographic variables and milk donation.

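### Donation is the main objective, but donation and five scores are all declared primary, and the 95% power applies only to one unnamed score

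*Protocol article*

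**What the plan says.** **Objectives.** Donation comes first: "The main objective of this study is to assess the effectiveness of an educational intervention based on TPB in breastfeeding mothers on donating breast milk". The secondary list includes "To evaluate changes in breastfeeding mothers’ knowledge about milk donation" and "To evaluate the effect of the educational program on behavioral determinants", the determinants being "attitude, subjective norms, perceived behavioral control and behavioral intention".

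**Data collection, and the Methods part of the abstract.** Donation and the scores are primary together: "Our primary outcomes are the number of mothers who have donated their breast milk and changes that have happened" in "knowledge, attitudes, subjective norms, perceived behavioral control about DHM and intention to donate milk". That is one yes/no outcome and five scores. Only the associations of determinants and demographic variables with donation are left as secondary outcomes.

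**Sample size.** The section opens "In order to provide a power of 95% with 95% confidence interval the following formula" and then uses a two-means formula with a difference of 3 and SDs of 3.21 and 3.17 from a cited study. It gives 30 per group, raised to 33 for 10% attrition. It names no score or time point and gives no donation rate.

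**Statistical analysis.** Chi-square or Fisher's exact test is named for qualitative variables, and repeated measures ANOVA for the effectiveness of the intervention. No order among the primaries and no success rule is given.

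**The concern.** Five measures are secondary in one section and primary in two other places, so the article does not settle what the trial must show. The named test of effectiveness, repeated measures ANOVA, suits the scores and not a yes/no outcome. The Discussion treats a rise in donation and in the scores as evidence of usefulness, but does not say what follows if scores rise and donation does not. The intervention could then be called effective while the main objective is missed.

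The sample size has a related gap. The only power figure belongs to a mean difference on one score. A reader who takes it as the power of the trial would read too much into a null result on donation.

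**Working it through.** **1. The plan's own figure**

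Inputs (Sample size section): z values 1.96 and 1.64, SDs 3.21 and 3.17, difference 3.

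- Sum of variances: 3.21² + 3.17² = 20.353.
- n = (1.96 + 1.64)² × 20.353 / 3² = 12.96 × 20.353 / 9 = 29.31. Unrounded z values give 29.39, matching the stated 29.4. Either rounds up to 30.
- Attrition: 30 + 3 = 33 per group, 66 in total.
- Power at 30 per group for this difference: 95.4%.

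The figure reproduces, but only for a comparison of two means on one score with individually independent mothers.

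**2. Family-wise error if any one primary suffices**

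Assuming independent tests, each at 5%:

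- Six primaries: 1 − 0.95⁶ = 0.265.
- Five scores alone: 1 − 0.95⁵ = 0.226.

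The scores come from one questionnaire, so correlation is likely. In a simulation with an assumed common correlation between the tests:

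| Correlation | Five tests | Six tests |
|---|---|---|
| 0 | 23% | 26% |
| 0.5 | 18% | 21% |
| 0.7 | 15% | 16% |

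**3. Error of donation's own test**

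Exact Fisher, two-sided 5%, 30 per group: the actual size is 0.2% if both arms donate at 5% and 0.9% if both donate at 10%. The test is conservative, and declaring other outcomes primary does not change that.

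**4. Power for donation**

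Exact two-sided Fisher test at 5% with 30 per group, the number expected to be analysed after attrition. Power is the sum of the binomial probabilities of all pairs of donor counts with p ≤ 0.05. Clustering is ignored. The donation rates are assumptions, because the article gives none.

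| Control vs intervention | Power |
|---|---|
| 0% vs 10% | 7% |
| 0% vs 20% | 57% |
| 0% vs 25% | 80% |
| 0% vs 30% | 92% |
| 0% vs 33% | 96% |
| 5% vs 20% | 24% |
| 5% vs 25% | 44% |
| 5% vs 30% | 63% |
| 5% vs 40% | 89% |
| 5% vs 45% | 95% |
| 10% vs 30% | 37% |

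For example, with no donors in the control arm the test needs at least 6 donors among 30 (5 of 30 gives p = 0.052; 6 of 30 gives p = 0.024). If the true rate is 25%, the chance of 6 or more is 80%.

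**The case against.** **A multiplicity rule may sit in a statistical analysis plan that is not shown.** This stands. The absence of an adjustment in a condensed article is not a fault by itself. What remains is the conflict between the Objectives and the list of primary outcomes, and a sample size resting on an unnamed score. The published text fixes both.

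**The 26% is an upper-end illustration.** This also stands. It needs independence, full 5% size in every test and an any-one-suffices rule. Donation under Fisher adds almost nothing, and correlation lowers the rest. A rule requiring success on all six would not inflate the error at all, but would cost power.

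**The article never attributes 95% power to donation.** This is true: the section does not say which outcome its power belongs to. That a null donation result would be presented as coming from a 95%-power trial is a risk and not something the text states.

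Three stronger readings are tempting but not supported:

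- *That donation's own type I error is inflated.* It keeps its nominal 5%, and less under Fisher.
- *That there are twelve tests, six outcomes at two follow-ups, with a 46% error (1 − 0.95¹²).* No separate test at each follow-up is described, and repeated measures ANOVA takes all time points of a score in one model.
- *That power should be read at 33 per group.* That is the recruitment figure; the plan's own calculation expects 30 to be analysed.

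**Conclusion.** The point holds as an inconsistency with consequences for inference. Donation is the main objective in one section and one of six equal primaries in others, with no success rule in this document. If any one primary sufficed, the family-wise error would be up to about 26%, and roughly 15% to 21% under the moderate to high correlations tried. The stated 95% power is correct for a 3-point difference on one unnamed score, ignoring clustering, and says nothing about donation.

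Power for donation depends on rates that the article does not give. Over the assumed range it reaches 95% only for very large effects, about 0% vs 33% or 5% vs 45%. The clustered design could lower power further; that loss is not included here.

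**What to change.** 1. In Data collection and the abstract, make donation by the final assessment the single primary outcome and the five scores secondary, in line with the Objectives.
2. In Sample size, name the score behind the 3-point difference and limit the 95% power statement to that score.
3. In the same section, state the donation difference detectable with 30 analysed per group, with the assumed control rate.

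If the sponsor prefers to keep several primaries, the alternative is to state a hierarchy or an alpha split and to amend the Objectives to match. An equal split over six (0.05/6 = 0.0083) would lower the power of the plan's own mean comparison at 30 per group from 95.4% to 84.2%; restoring 95% would take 42 per group.

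The cost of the recommended change is wording in the protocol and the matching registry entry, with no extra mothers. The downside is a less favourable stated power for the main objective and less formal weight for the score results.
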